### 2.6. Intervention Groups

In this three-arm RCT, two regimens of nutritional intervention, Bifidobacterium plus perilla oil and Bifidobacterium alone, will be compared to the control group. These two interventions will be completed within 12 weeks of the random allocation of the interventions. We have chosen perilla oil, which is rich in ALA, as an omega-3 supplement based on our observational and other studies. Consumption of a diet rich in ALA facilitates the inhibitory learning of original fear memories more than a diet rich in linolenic acids, one of the n-6 PUFAs, in rats [36]. An ALA-rich chocolate milkshake was recently found to facilitate the inhibitory learning of original fear memories in healthy individuals [37].

Participants in the Bifidobacterium plus perilla oil group will be asked to take 2 capsules (10 billion Bifidobacterium bacteria per capsule) and 1 sachet containing 3 g perilla oil (1.8 g ALA) daily with meals. Perilla oil may be mixed with soup or poured over salad or yogurt. Participants in the Bifidobacterium group will be asked to take 2 capsules (10 billion Bifidobacterium bacteria per capsule) with breakfast. Although there will be no restriction on concomitant drugs/treatments/procedures, information regarding concomitant drugs/therapies during the study will be collected as study data.

To enhance treatment adherence, participants will be contacted by telephone or email at 0, 4, 8, and 12 weeks of the study period. Participants will be informed that if they forget to take a capsule or sachet, they can take a 2-day dose at one time. They will be instructed not to chew the Bifidobacterium capsules. Participants in the intervention groups will be asked to report the number of weeks (0–12) that they have been taking their capsules and sachets during the 12 weeks and the reasons why they did not take them if they took ≤7 (i.e., compliance rate <60%).

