### 2.12. Harm

Adverse reactions (ARs) will be collated as secondary outcomes. At 12 weeks after random allocation, we will specifically ask if participants have had any of the following ARs: headache, nausea, diarrhea, loose stool, and burping (if any, we will also ask about the time of onset, severity, subjective severity, need for treatment, and prognosis). The ARs of the participants in the intervention group will be monitored over the telephone by the CRC at 4 and 8 weeks after entry into the study. This step is based on previous studies reporting an 18% increased risk of ARs with omega 3 supplements compared to a placebo. The most common ARs were gastrointestinal and included nausea, diarrhea, and other minor gastrointestinal disturbances [44]. Clinical trials using Bifidobacterium have been conducted with only small sample sizes, and the ARs remain unclear.

An Efficacy and Safety Committee will be established, comprising an independent chair and at least two independent members. In the event of a serious illness for which a causal relationship to the intervention cannot be ruled out, this Committee will convene. If three serious illnesses for which a causal relationship to the intervention cannot be ruled out occur, the study will be stopped immediately without waiting for review by the Committee. The treatment of and care for ARs in patients enrolled in the study are covered by their medical insurance.

Participants who experience a substantial worsening of FCR or depressive symptoms during the study period will be promptly referred to a psychiatrist in collaboration with their physician. All of the test foods used in this study are commercially available and are well-established dietary products. Therefore, this study will not be covered by clinical research insurance. In the unlikely event that a research subject suffers health problems as a result of participation in this study, appropriate measures will be taken to provide the necessary treatment, including examination and treatment, within the research subject’s insurance coverage.

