The following secondary and sensitivity analyses will be performed for additional discussion of the primary analysis, which will determine the need for further studies. These analyses will be conducted after the primary analysis is completed. For all continuous outcomes (CARS, PHQ-9, IBS-SI, and gut microbiome composition), differences in the scores at 12 weeks and changes between baseline and 12 weeks will be examined using non-paired t-tests and mixed-effect models for repeated measures analysis using repeated timepoints and age, disease duration, and hospital as covariates. For dichotomous or dichotomized categorical outcomes such as ARs and proportion of participants with a moderate or high level of FCR at 12 weeks, relative risk will be calculated. Chi-squared and Fisher’s exact tests will be used for statistical significance testing. The aforementioned analyses will be performed between the combined intervention group (those treated with Bifidobacterium alone and those treated with Bifidobacterium plus perilla oil; *n* = 30) and the control group (*n* = 15). The purpose of this analysis is to increase the power of the hypothesis test to examine whether Bifidobacterium intervention is effective against FCR. This is a supplemental analysis to reinforce the arguments of the primary analysis. Furthermore, to explore the association of changes in symptoms with the gut microbiome and PUFAs, we will perform correlation analyses.

This study will not include an interim analysis. If either of the intervention groups (Bifidobacterium alone and Bifidobacterium plus perilla oil) are inferior to the usual treatment group (control group), it is not a matter of concern whether it is statistically significant or not, so the test will be one-sided. The significance level of the entire test is 2.5% for one side. While this decision might lead to errors in multiple tests, this will be the first study of nutritional intervention for FCR. Therefore, we consider the avoidance of beta errors to be preferable over alpha errors. However, 95% confidence intervals will be presented for differences among groups.

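### The planned relative risk for adverse reactions is not clearly limited to the week-12 checklist common to all arms, although only the intervention groups are also monitored at weeks 4 and 8

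*Protocol article*

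**What the plan says.** ARs have outcome status in section 2.12: "Adverse reactions (ARs) will be collated as secondary outcomes". The same section describes two ways of collecting them.

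- **Week 12, no arm restriction.** "At 12 weeks after random allocation, we will specifically ask if participants have had any of the following ARs", followed by five named symptoms and a request for details such as time of onset and severity.
- **Weeks 4 and 8, intervention only.** "The ARs of the participants in the intervention group will be monitored over the telephone by the CRC at 4 and 8 weeks" after entry. The reason given is an 18% higher AR risk reported for omega-3 supplements against placebo.

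Section 2.8 (Control Group) describes no scheduled interim contact; information is supplied when a participant enquires. Table 1 places ARs at the outcome assessment, with a line for collection as needed.

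Section 2.14 then plans the comparison. "For dichotomous or dichotomized categorical outcomes such as ARs and proportion of participants with a moderate or high level of FCR at 12 weeks", a relative risk is to be calculated, and "Chi-squared and Fisher’s exact tests will be used for statistical significance testing". It continues: "The aforementioned analyses will be performed between the combined intervention group" (n = 30) and the control group (n = 15). Nothing there says which AR records are counted.

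**The concern.** An RR for harms can be interpreted only if events had the same chance of being recorded in each arm. Here a treated participant faces three scheduled AR enquiries and a control faces one, which looks back over 12 weeks. The listed symptoms (headache, nausea, diarrhea, loose stool, burping) can be minor and may be forgotten by week 12. If all reports are counted together, the extra enquiries raise the recorded incidence in the intervention groups whether or not the products cause anything.

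The trial is meant to inform a phase III study, and section 2.12 itself says that the ARs of *Bifidobacterium* remain unclear. An RR inflated by the collection schedule would pass into that evidence as if it were a product effect.

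**Working it through.** **The plan's own figures.** The protocol gives no expected AR rate, capture probability or power for ARs. Its sample size in section 2.13 concerns the recurrence-fear score (CARS). It reproduces: exact t-test power is 88.4% with 10 per group and 91.4% with 11, hence 11, plus 4 dropouts = 15 per group. It does not bear on this point. The only AR benchmark is the 18% increase in section 2.12, an RR of about 1.18.

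**Assumptions.** True incidence is equal in all arms, with one event per affected participant. Each enquiry after onset captures the event with probability q, independently of the others. The values q = 0.5 and q = 0.7 are illustrative and do not come from the documents. All reports are pooled.

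**Capture in controls:** q (week 12 only).

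**Capture in the intervention groups, by time of onset:**

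- after week 8, one enquiry: q
- between weeks 4 and 8, two enquiries: 1 − (1 − q)²
- before week 4, three enquiries: 1 − (1 − q)³

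| | q = 0.5 | q = 0.7 |
|---|---|---|
| One enquiry | 0.500 | 0.700 |
| Two enquiries | 0.750 | 0.910 |
| Three enquiries | 0.875 | 0.973 |
| Mean, onset spread evenly | 2.125/3 = 0.708 | 2.583/3 = 0.861 |
| Apparent RR, even onset | 0.708/0.5 = 1.42 | 0.861/0.7 = 1.23 |
| Apparent RR, all onset before week 4 | 0.875/0.5 = 1.75 | 0.973/0.7 = 1.39 |

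With no product effect there is no reason for symptoms to cluster before week 4, so the even-onset row is the more reasonable illustration and the last row is the upper case under this model.

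**Effect on the test.** This is a separate illustration. Total capture is set at 90% in the intervention groups and varied in controls; Fisher's exact test is taken as one-sided at 2.5% in the direction of excess ARs, with 30 against 15 and no true difference.

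| Control capture | Apparent RR | Rejection rate, true risk 20% | Rejection rate, true risk 40% |
|---|---|---|---|
| 50% | 0.9/0.5 = 1.80 | 1.7% | 10.3% |
| 70% | 0.9/0.7 = 1.29 | 0.9% | 3.5% |
| 90% | 0.9/0.9 = 1.00 | 0.5% | 1.1% |

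Unequal capture raises the false-positive rate relative to the last row. It passes the nominal 2.5% only at the higher true risk. In a trial of this size the main damage is to the estimate rather than to the test.

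**If only the week-12 checklist is counted,** capture is q in every arm under the first model, and the expected RR with no true difference is q/q = 1.0.

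**The case against.** The strongest reply is that the comparison was never meant to include the interim calls. Section 2.12 first describes the week-12 checklist, which asks everyone to look back and date the onset, and only then mentions the calls, as monitoring with a safety reason. Table 1 has no week-4 or week-8 column for ARs. No passage says that the calls feed the RR, and the choice of records for a secondary table is often left to an analysis plan, which is not shown here.

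Part of this stands. Pooling is not stated, so the bias is conditional. But the protocol itself fixes both the unequal schedule and the between-group test. It says that ARs are collated, without separating the sources. In section 2.14 the reference to 12 weeks most naturally attaches to the proportion with moderate or high fear, not to ARs. A plan that creates unequal data and then tests them against control should say which data are tested. Closer monitoring of treated participants is not itself at fault.

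Three stronger readings are tempting and are not supported:

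- **That the RR will exceed 1.** This needs both pooling and imperfect recall at week 12, and with 45 participants chance can put the observed value on either side of 1.
- **That 1.75 to 1.39 is the likely size.** It requires every event to occur before week 4 and the enquiries to be independent. Someone who reports a symptom at week 4 may well report it again at week 12, and evenly spread onset brings the range down to 1.42 to 1.23.
- **That the same calls bias the primary fear outcome through extra staff attention.** Section 2.6 says "To enhance treatment adherence, participants will be contacted by telephone or email at 0, 4, 8, and 12 weeks", so those contacts serve adherence to the intervention, and the documents do not say that they are the AR calls. The Discussion already discloses that the effect may be overestimated without a placebo. That is a separate design question.

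**Conclusion.** The point holds in conditional form. AR ascertainment at weeks 4 and 8 is unequal by design, and the planned RR and tests are not clearly limited to the information collected alike in all arms. If the interim reports are counted, the RR against control is expected to be biased upward with no true difference.

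The direction follows from the schedule, provided that recall at week 12 is incomplete; the size cannot be established from the documents. On the assumed capture probabilities of 0.5 to 0.7, evenly spread onset gives 1.42 to 1.23. Even the lower figure exceeds the RR of about 1.18 that the protocol cites as its reason for the calls, so the artefact could be as large as the signal of interest.

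The primary analysis and the sample size are untouched. This is a secondary outcome in an exploratory trial: worth correcting because the correction is easy, but not a serious defect.

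**What to change.** State in section 2.14, or in the analysis plan, that the between-group relative risk and the chi-squared and Fisher's exact tests for ARs use only the week-12 checklist asked identically in all arms. Report the week-4 and week-8 monitoring findings descriptively for the intervention groups, without a test against control.

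The cost is a sentence or two. No sample size, visit or primary analysis changes, and the monitoring calls continue as planned. There is a small downside: some early events recorded only at weeks 4 or 8 drop out of the comparison, although the descriptive report still shows them. Some bias may also remain, because earlier calls can prompt recall at week 12 and participants know whether they are taking the products. The report should say so.

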### 2.13. Sample Size Calculation

The sample size was estimated based on power analysis using the CARS score. To our knowledge, no previous reports have examined the effects of nutritional interventions on FCR, so there is no reference on which we can base our power calculation.

In our observational study conducted between 2017 and 2018, the mean CARS score of a subset of breast cancer survivors who met the eligibility criteria for this study with a prior history of chemotherapy and CARS score ≥3 was 3.96 (SD ± 0.67). Furthermore, in this study, the intervention will be considered clinically significant if the mean CARS score at week 12 in the intervention group is 1 point lower than the mean CARS score at week 12 in the control group. The CARS score ranges from 1 (not worried at all) to 6 (always very worried). In the opinion of breast surgery specialists (TK and AM), a 1-point decrease in this score from 4 (somewhat worried) to 3 (slightly worried) is clinically significant.

Thus, based on the above hypothesis and the results of our previous study, the mean difference in CARS scores was estimated to be 1.0 ± 0.67 (SD) between the Bifidobacterium plus perilla oil group and the control group and between the Bifidobacterium and the control groups at 12 weeks after random allocation. To detect the difference between the two groups, using unpaired *t*-tests with a one-sided alpha of 2.5% and power of 90%, the calculation showed that 11 participants per group would be required in the analysis population. This was calculated using G*Power software (ver.3.1.9.4). Assuming 4 dropouts per group, 15 participants will be enrolled per group (45 in total).

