## 2. Methods and Analysis

### 2.1. Study Design

This study has been planned as an exploratory clinical study (phase 2) and will be conducted as a three-arm, 12-week parallel group, masked-rater randomized controlled trial (RCT). The study is registered in the Japan Registry of Clinical Trials (jRCT; Trial ID jRCTs031200029). Participants will be randomized with 1:1:1 allocation to receive Bifidobacterium plus perilla oil, Bifidobacterium alone, or no intervention (control). A total of 15 participants will be allocated to each arm. These interventions will end within 12 weeks of the registration of each participant. The primary outcome will be FCR severity at 12 weeks as assessed by masked raters using the 4-item Concerns about Recurrence Scale (CARS) that asks about overall fear of recurrence.

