### 2.2. Inclusion Criteria

Aged 20 years or older at the time of providing informed consent;Outpatient at the National Center of Neurology and Psychiatry hospital or the National Hospital Organization Tokyo Medical Center;Histologically or cytologically confirmed invasive breast cancer without cancer recurrence. The criteria is limited to invasive breast cancers because they are more likely to recur than non-invasive breast cancers and tend to be associated with a higher level of (more severe) FCR;Chemotherapy completed at least 6 months before registration. Hormone therapy may be ongoing. Patients who have only just completed chemotherapy will not be included because their diets tend to change due to stomatitis, and their gut environment can be unstable due to acute intestinal inflammation from the chemotherapy;At least a moderate level of fear (scoring ≥ 3 points) for the item of intensity of fear on the CARS, as previously reported by studies using the CARS [32,33];Recognition of cancer diagnosis. This criterion is set because a small number of people do not recognize themselves as having cancer, but the patients in the present study must recognize themselves as cancer survivors.

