### 2.10. Primary Outcome Measures

The primary outcome will be FCR severity at 12 weeks as assessed by the masked raters using the 4-item CARS. The CARS comprises 30 questions [33] of which 4 concern overall fear of recurrence; the remaining 26 questions measure worries associated with recurrence under specific circumstances such as “worries about female sexuality” and “worries about future treatment”. These 26 questions will not be asked in this study. The 4 questions regarding overall fear of recurrence address the frequency, potential for upset, consistency, and intensity of fear. Each question is scored from 1 (no fear) to 6 (intense/frequent fear), giving an average score of 1 to 6, with higher scores indicating greater fear of recurrence. The validity of the Japanese version has been confirmed [40]. Participants who score ≥3 on overall fear of CARS will be categorized as having a moderate or high level of FCR [32,33].

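### The planning SD of 0.67 comes from a baseline sample selected for CARS ≥3 and is used unchanged for the unrestricted week-12 score, so 90% power with 11 analysed per arm is probably optimistic

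*Protocol article*

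**What the plan says.** Section 2.13 takes its SD from the sponsor's observational study, in breast cancer survivors who met this trial's eligibility criteria "with a prior history of chemotherapy and CARS score ≥3 was 3.96 (SD ± 0.67"). It then applies the same SD to the difference between each intervention group and control at 12 weeks: "the mean difference in CARS scores was estimated to be 1.0 ± 0.67 (SD"). The calculation is made "using unpaired *t*-tests with a one-sided alpha of 2.5% and power of 90" percent, and concludes that "11 participants per group would be required in the analysis population". Enrolment follows from that: "Assuming 4 dropouts per group, 15 participants will be enrolled per group (45 in total").

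Three other places bear on the SD:

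- Section 2.2 sets the fear criterion for entry on one item: "At least a moderate level of fear (scoring ≥ 3 points) for the item of intensity of fear on the CARS".
- Section 2.10 defines the outcome as the mean of four items, "giving an average score of 1 to 6, with higher scores indicating greater fear of recurrence". It also uses a cut of 3 on overall fear to classify participants, so the article contains two different ≥3 rules.
- Section 2.14 makes the primary test an unpaired t-test on week-12 scores, without adjustment for baseline.

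The article gives no week-12 SD, no SD in an unselected sample and no correlation between repeated CARS scores.

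**The concern.** A sample kept only if it scores 3 or more has lost its lower tail, so its SD is smaller than that of the population it came from. When the same people are measured again 12 weeks later, nothing keeps their scores at 3 or above. Unless the two measurements correlate perfectly, some scores fall back below 3 and the spread widens. The planned effect adds to the doubt: a 1-point benefit takes the treated mean from 3.96 to about 2.96, which is at the cut itself. About half of the treated scores would then lie in a region that the planning sample seems to have excluded.

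The unadjusted t-test depends on the week-12 SD, so a planning SD that is too small makes the stated power too high. Section 2.14 says the trial is meant to inform a phase III study and that avoiding beta errors has priority over avoiding alpha errors. If the beta error is larger than the 10% stated, a null result could be given more weight against a 1-point effect than it deserves.

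**Working it through.** **Inputs from the article.** Difference 1.0, SD 0.67, one-sided alpha 2.5%, 11 analysed and 15 enrolled per arm (2.13); "Participants will be randomized with 1:1:1 allocation" (2.1); outcome a mean of four items on 1 to 6 (2.10). If each item is a whole number, the mean moves in steps of 0.25.

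**Step 1: reproduce the stated figure.** Power is from the noncentral t distribution with 2n − 2 degrees of freedom and noncentrality 1.0 / (SD × √(2/n)). With SD 0.67 the standardised difference is 1.0 / 0.67 = 1.49. Power is 88.4% at n = 10 and 91.4% at n = 11, so 11 per arm is correct for these inputs.

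**Step 2: how much slack there is.** Solving for the SD at which power equals 90% gives 0.688 with 11 per arm and 0.815 with 15 per arm. The first is only 0.688 / 0.67 − 1 = 2.7% above the planning value.

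| Week-12 SD | Power, 11 per arm | Power, 15 per arm | n per arm for 90% |
|---|---|---|---|
| 0.67 | 91% | 98% | 11 |
| 0.75 | 84% | 94% | 13 |
| 0.80 | 80% | 91% | 15 |
| 0.90 | 70% | 84% | 19 |

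**Step 3: what week-12 SD is plausible if the cut was on the 4-item score.** Assume a normal score recorded in 0.25 steps, of which only values of 3 or more are kept. The parent distribution that then gives mean 3.96 and SD 0.67 has mean 3.71 and SD 0.85. Let r be the baseline-to-week-12 correlation in that parent, with the same parent SD at both times. The week-12 SD in the selected people is

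√(r² × 0.67² + (1 − r²) × 0.85²).

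The article gives no r, so a range is used.

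| Assumed r | Week-12 SD | Power, 11 per arm | Power, 15 per arm |
|---|---|---|---|
| 0.5 | 0.81 | 79% | 90% |
| 0.7 | 0.77 | 83% | 93% |
| 0.9 | 0.71 | 88% | 96% |

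If trial entry is on the intensity item while 0.67 came from a cut on the mean, people with a 4-item mean below 3 can also enter. With an assumed item-to-mean correlation of 0.8 to 0.9 and essentially the same parent (SD 0.846), the week-12 SD is 0.71 to 0.82 and power at 11 per arm is 77% to 88%, so this changes little.

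**Step 4: the other reading of the subset.** If 0.67 already comes from selection on the intensity item, the mean score was cut less sharply. With the same assumed correlations, the parent SD is 0.72 to 0.85, the week-12 SD 0.68 to 0.81 and power at 11 per arm 79% to 91%. When the whole-number scoring of the item is allowed for (cut at 2.5), the week-12 SD is 0.68 to 0.71 and power 88% to 91%.

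**Step 5: what baseline adjustment would recover.** Under the Step 3 model, the SD left after adjusting for baseline is 0.85 × √(1 − r²). At r = 0.5 this is 0.74, and at r = 0.6 it is 0.68. With one degree of freedom spent on the covariate, power at 11 per arm is about 85% and 90% respectively, and higher for larger r.

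**The case against.** The strongest objection is that the mismatch between samples is not established. The subset is said to have met this trial's eligibility criteria, and the fear criterion among these is the intensity item. The reference to a CARS score of 3 or more may be shorthand for that item. A reader might infer that the planning sample was certainly cut on the 4-item mean and so differs from the trial population. The article does not settle this, and on the item reading the shortfall can vanish (Step 4). This part of the objection stands.

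Second, the size rests on an assumed distribution and correlation. A reader might infer that power could be as low as 61%. That figure needs a week-12 SD of 1.00, which results from treating the score as continuous between 3 and 6 (parent SD 1.09) together with the lowest correlation, 0.5. The outcome is a four-item mean, and the quarter-point calculation does not reach that value. The 61% should not be used.

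Third, 11 is the number left after losing 4 of 15 per arm. The per-protocol rule in 2.14 asks for only 4 of 12 weeks of intake, so more than 11 may be analysed. Under Step 3, 90% is kept if all 15 are. It would therefore be wrong to say that the trial as enrolled cannot reach 90%. The claim in 2.13, however, is made for 11.

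Fourth, the trial is exploratory, no earlier nutritional trial on this outcome was known to the sponsor, and 95% confidence intervals are promised. The intervals will show directly whether a 1-point effect is excluded, which limits the harm from an optimistic power figure. It does not make that figure right.

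**Conclusion.** The sample size arithmetic is correct; the weakness is the SD put into it. A baseline SD from a sample selected from below is used for a later score that has no lower cut, and the article gives no reason for carrying it over. The direction follows from the selection. With only 2.7% of slack in the SD, 90% power at 11 analysed per arm is probably optimistic.

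The best estimate of the size is a week-12 SD of about 0.71 to 0.81 and power of about 79% to 88% at 11 per arm, or 90% to 96% at 15. It rests on a normal parent cut at 3 on the quarter-point scale and a correlation of 0.5 to 0.9, neither of which is in the article. If selection was on the intensity item, the loss may be negligible. The point is worth correcting, but it does not invalidate the design.

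**What to change.** In 2.13:

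- State whether the 4-item mean or the intensity item defined the ≥3 subset that gave 0.67.
- Say that 0.67 comes from a range-restricted sample at a single time point.
- Replace the flat 90% with power over a range of week-12 SDs, for example 0.67 to 0.90: 91% down to 70% with 11 per arm, and 98% down to 84% with 15.

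In 2.14, make the primary comparison of week-12 CARS an analysis of covariance with baseline CARS as covariate, and state the same test in 2.13. Baseline CARS is already collected before allocation.

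The changes to 2.13 cost a paragraph and a less favourable power statement. The change to 2.14 is more than rewording: it replaces the primary test, and section 3.1 requires a formal amendment for changes to the analyses. It should be made before outcome data are seen. No patients or assessments are added.
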